#### Analysis

The primary outcomes of feasibility, acceptability, and usability will be assessed descriptively. We will compare ART-related decisional conflict, clinic attendance, viral suppression, and medication refills between and within the 90 women in each arm (baseline vs postvisit surveys and EMR data at 3 and 6 months). For normally distributed data, we will first use *t* tests to compare the 2 arms and then use regression methods to develop a multivariable model of the outcome, with arm membership as the principal covariate, while controlling for the moderators listed in the previous sections and in Table 2. For nonnormally distributed data, we will employ chi-square tests and logistic regression; distributional properties of the outcome will determine the type of logistic regression (eg, binary, multinomial, or ordinal logistic regression models). We note that these are examples and the final approach will be determined based on the distribution of the data.

The primary analysis will use an intent-to-treat approach with the use of *i.ARTs* as a 1-time exposure, with α=.05, and 2-sided tests. The number of moderators included in the regression model will be used to make a Bonferroni adjustment to the α value. A secondary efficacy analysis will explore actual treatment taken. Our exploratory tertiary outcomes of viral suppression, clinic attendance, chosen ART modality, and medication refills will compare both between and within *i.ARTs* and control arm women (ie, baseline and postvisit surveys and EMR data at 3 and 6 months); we will also examine these outcomes for women who do not change regimens. We will use prebaseline EMR data to control for previous viral load. We will also compare how many women in each arm change modalities postbaseline to assess *i.ARTs’* accuracy in identifying which HIV treatment modality is the best match. Sensitivity analyses will determine whether assumptions associated with each model are defensible.

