#### Study Outcomes and Measures

All study outcomes are summarized in Table 2. *Primary outcomes* include *i.ARTs feasibility, acceptability,* and *usability.* To assess feasibility, we will adapt Thabane et al’s [59] framework [60,61]. For *acceptability and usability,* we will use the 8-item Client Satisfaction Questionnaire (CSQ-8) to assess participants’ attitudes, burden, ethics, coherence, opportunity cost, perceived effectiveness, and self-efficacy [63]. The *secondary outcome* is ART-related decisional conflict, a 16-item scale scored from 0 to 100 [52]. Scores of 0-25 are associated with “implementing decisions” and scores of 37.5-100 are associated with “decision delay/feeling unsure.” *Tertiary outcomes* are exploratory, and consist of information extracted from EMRs, including viral suppression at the most recent visit in the prior 6 months, ART modality, medication refills (oral ART), and clinic attendance in the prior 6 months.

In addition to the outcomes, the baseline survey will measure moderators associated with adherence, including sociodemographics, depression, anxiety, substance use, HIV-related stigma and discrimination, self-efficacy, and ART-related knowledge.

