#### Power Analysis and Sample Size

Our sample size is based on our secondary outcome of decisional conflict, as our primary outcomes of acceptability and feasibility are only assessed in the intervention group (as the control group will not experience *i.ARTs*). Scale developers use a moderate effect size (0.3-0.4) to determine sample size. Using the average weighted means and SDs from prior studies [52], we calculated sample size for α=.05, power=0.8 for an independent samples *t* test. Assuming a mean score of 21 (SD 16) in the intervention (*i.ARTs*) group and a mean score of 28 (SD 18) in the control group, the sample size of 90 in each group, for a total of 180, provides 80% power. Our tertiary outcomes are exploratory, but as 35% of US women are not adherent after 6 months, we are powered to detect basic differences between the intervention and control arms.

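### The rule for nonnormal outcomes could lead to categorizing decisional conflict, the score on which the trial is sized, and so cost power; its analysis on the 0-100 scale should be fixed in advance

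*Protocol article*

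**What the plan says.** The Analysis section of the protocol article lists decisional conflict, clinic attendance, viral suppression and medication refills as outcomes to be compared between and within arms. It then divides the methods by distribution:

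- For normal data it uses t "tests to compare the 2 arms and then use regression methods to develop a multivariable model of the outcome".
- For the rest: "For nonnormally distributed data, we will employ chi-square tests and logistic regression". The type of logistic model depends on the outcome's distribution ("eg, binary, multinomial, or ordinal logistic regression models").
- It closes with a qualification: "We note that these are examples and the final approach will be determined based on the distribution of the data".

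Tests are run "with α=.05, and 2-sided tests". No rank-based, robust or bootstrap method for a continuous but skewed outcome is named.

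Study Outcomes and Measures describes decisional conflict as "a 16-item scale scored from 0 to 100". It gives 0-25 and 37.5-100 as interpretive bands and does not say that the outcome will be banded.

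Power Analysis and Sample Size sizes the trial on this secondary outcome with an independent-samples t test: "Assuming a mean score of 21 (SD 16) in the intervention" arm against 28 (SD 18) in the control arm, with 90 per arm said to give 80% power.

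**The concern.** The rule treats nonnormal as if it meant categorical. That is harmless for viral suppression, which is binary by definition. It does not suit a continuous score: a chi-square test and a binary or multinomial logistic model need categories, and decisional conflict has them only if someone cuts it.

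The rule is likely to matter for this outcome, because the plan's own means and SDs are hard to reconcile with a normal distribution on a scale that cannot go below 0. Three things are at stake:

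- **Power.** Cutting the score discards information in the one outcome that determined the sample size.
- **Estimand.** The target would change from a difference in means, for which the trial was sized, to a difference in proportions or an odds ratio.
- **Prespecification.** The test and any cut-point could be chosen after the outcome distribution is seen, in a trial where the researchers are not blind to arm (Randomization section).

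**Working it through.** **Inputs.** From Power Analysis and Sample Size: means 21 and 28, SDs 16 and 18, 90 per arm. From Analysis: two-sided α = 0.05. From Study Outcomes and Measures: range 0-100, thresholds 25 and 37.5. The shape of the distribution is not given. It is assumed, and varied below.

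**1. The plan's own figure.**
- Pooled SD = √((16² + 18²)/2) = √290 = 17.03. Standardized difference = 7/17.03 = 0.41.
- Standard error = 17.03 × √(2/90) = 2.54. Power ≈ Φ(7/2.54 − 1.96) = Φ(0.80) = 78.7%. The noncentral t gives 78.3%.
- The stated 80% is therefore reproduced to within 2 points. A full 80% needs 93 per arm.

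**2. Is the score likely to be skewed?**
- Distance from floor to mean: 21/16 = 1.31 SD and 28/18 = 1.56 SD.
- Normal curves with these values would put Φ(−1.31) = 9.5% and Φ(−1.56) = 6.0% of scores below 0, which is impossible on this scale.
- A beta distribution on 0-100 matched to the means and SDs has skewness 0.97 (intervention) and 0.68 (control). A matched gamma has 1.52 and 1.29.
- In simulated trials of 180 women from either skewed distribution, a Shapiro-Wilk test on the residuals rejected normality every time. The plan names no such test, so this shows only that skew of this size would be visible.

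**3. Power if the score is cut in two.** Let p₁ and p₂ be the proportions at or below the cut, p̄ their average, and n = 90. Then power = Φ[(|p₁ − p₂| − 1.96·√(2p̄(1−p̄)/n)) / √((p₁(1−p₁) + p₂(1−p₂))/n)].

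Example, beta at 25: (0.1623 − 1.96 × 0.0736)/0.0726 = 0.25, and Φ(0.25) = 60%.

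| Distribution | Cut | Intervention | Control | Power | n per arm for 80% |
|---|---|---|---|---|---|
| Beta | 25 | 66.1% | 49.9% | 60% | 145 |
| Beta | 37.5 | 84.0% | 71.9% | 50% | 183 |
| Gamma | 25 | 68.7% | 51.8% | 64% | 130 |
| Gamma | 37.5 | 86.1% | 75.4% | 44% | 213 |
| Normal (reference) | 25 | 59.9% | 43.4% | 60% | 144 |
| Normal (reference) | 37.5 | 84.9% | 70.1% | 66% | 125 |

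**4. Other routes, by simulation** (5,000 trials per distribution, 90 per arm; the three bands are 0-25, between, and 37.5-100):

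| Analysis | Beta | Gamma |
|---|---|---|
| t test, full score | 78% | 79% |
| Rank test, full score (equivalent to the score test of an ordinal logit) | 79% | 86% |
| Ordinal test, three bands | 63% | 65% |
| Chi-square, three bands | 53% | 54% |

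Under a matched beta with no difference between arms, the t test rejected in about 5% of trials. Skew of this degree therefore gives no reason to abandon the comparison of means at 90 per arm.

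No dropout was applied, because none is stated. The Bonferroni adjustment described in Analysis was not applied either; a smaller α would lower every figure.

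**The case against.** The strongest reply is that the plan does not say decisional conflict will be categorized. The sentence setting out the rule also offers ordinal logistic regression, which can use the whole score. The methods are called examples. No cut-point and no normality test is named, and the bands at 25 and 37.5 appear only as interpretation of the scale. The rule covers a mixed list that includes viral suppression and attendance, so nonnormal may be loose wording for categorical. Read with the sample-size section, a t test may be what is intended. Decisional conflict is also a secondary outcome in a pilot whose primary outcomes are descriptive, and a journal article may leave the final model to an analysis plan.

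Most of this stands as a limit on the claim. A reader might infer that the score will be cut and that power will drop to 50-60%. The documents do not support that: a full-score ordinal analysis is allowed and loses no power, and 50-60% corresponds to one assumed distribution at particular cuts.

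The reply does not remove the point. The article states a rule, and the rule as worded covers the sizing outcome. Chi-square is named first for nonnormal data, and nothing says that an ordinal model would use the full score rather than bands. Calling the methods examples leaves the choice open until the data are seen, which is part of the difficulty.

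**Conclusion.** The point holds as a risk created by the wording. Skew in decisional conflict is very likely on the plan's own planning values, although the document does not state it, and the stated rule could then move the outcome from the t test used for sizing to a categorical analysis. If the score were cut at 25 or 37.5, power at 90 per arm could fall from about 78% to roughly 45-65%: 44-64% for two-way splits under the skewed distributions, and 53-54% for a three-band chi-square test. A split at 25 under those distributions would need about 130-145 per arm for 80% power.

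These figures rest on the stated means and SDs, on assumed beta and gamma shapes, on cut-points that the plan mentions but does not adopt for analysis, and on no dropout and no multiplicity adjustment. That the score will be categorized, or that any one power figure will apply, cannot be concluded from the document. Since this outcome alone determined the sample size, the wording should be tightened.

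**What to change.** In the Analysis section, take decisional conflict out of the distribution-dependent rule and state in advance:

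- It is compared between arms on its continuous 0-100 scale whatever its observed distribution, by a t test or by a linear model with robust standard errors or a bootstrap confidence interval. One of these is named as the main analysis.
- A rank-based or full-score proportional-odds analysis is the sensitivity analysis.
- The 25 and 37.5 bands are reported descriptively only.
- Chi-square tests and binary or multinomial logistic regression are kept for outcomes that are categorical by definition, such as viral suppression.

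The cost is a change of wording in the protocol and any analysis plan, made before outcome data are examined. It needs no extra participants or data collection, and it brings the analysis into line with the t test on which the 90 per arm was calculated.

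### Decisional conflict, the outcome that sizes the trial, gets a between-arm t test, a later multivariable model and within-arm comparisons; none is named as deciding, and the within-arm ones do not test i.ARTs

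*Protocol article*

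**What the plan says.** The Analysis section deals with the primary outcomes first: "The primary outcomes of feasibility, acceptability, and usability will be assessed descriptively". Power Analysis and Sample Size adds that the "primary outcomes of acceptability and feasibility are only assessed in the intervention group", so no between-arm test of them is possible. The tertiary outcomes are called exploratory. That leaves decisional conflict, the secondary outcome, as the one the trial is built to test: "Our sample size is based on our secondary outcome of decisional conflict", with an independent-samples t test at α=.05.

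For that outcome the Analysis section lists several comparisons:

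- Between and within arms: "We will compare ART-related decisional conflict, clinic attendance, viral suppression, and medication refills between and within the 90 women in each arm", using the baseline and postvisit surveys.
- Two between-arm steps for normally distributed data: "tests to compare the 2 arms and then use regression methods to develop a multivariable model of the outcome", with arm as the principal covariate and the Table 2 moderators as controls. The section calls these methods examples and leaves the final approach to the distribution of the data.
- An error rate: "The primary analysis will use an intent-to-treat approach with the use of" i.ARTs "as a 1-time exposure, with α=.05, and 2-sided tests". The next sentence applies a Bonferroni adjustment based on how many moderators enter the regression.

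No sentence in either section says which comparison decides whether i.ARTs reduced decisional conflict.

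**The concern.** Three kinds of result could be read as the answer, and they can disagree. The t test and the multivariable model estimate the same arm effect and can fall on opposite sides of .05.

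The within-arm comparisons are a different matter, because they do not estimate the effect of i.ARTs at all. By the Assessments section, the second survey follows the clinic visit in both arms. By the Randomization section, control women are offered information about LAI ART from their provider. Decisional conflict may therefore fall in both arms whether or not the tool works. A significant fall in the i.ARTs arm, or a fall significant there but not in control, could then be reported as an effect that the randomised comparison does not show.

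The only multiplicity adjustment stated divides α by the number of moderators, not by the number of tests of i.ARTs. It is also unclear whether it applies to the arm term. If it does, the α in the model differs from the α on which the trial was sized.

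**Working it through.** **1. The plan's own figure.** Inputs from Power Analysis and Sample Size: means 21 (SD 16) and 28 (SD 18), 90 per arm, two-sided α=.05.

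- Pooled SD = √((16² + 18²)/2) = √290 = 17.03
- d = 7/17.03 = 0.411
- Noncentrality = 7/(17.03 × √(2/90)) = 2.76
- Power = 0.783 (noncentral t) or 0.787 (normal approximation)

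The stated 80% is reproduced to within 2 points. It holds for one between-arm t test at the full .05.

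**2. Within-arm test when i.ARTs has no effect.** Assumptions, since the documents give neither: both arms fall equally by f = 0.2 or 0.3 SD (0.2 × 17.03 = 3.4 and 0.3 × 17.03 = 5.1 points), with baseline-post correlation ρ = 0.5.

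- SD of change, in SD units = √(2(1 − ρ)) = 1.00
- Noncentrality of the paired test, n = 90: f × √90 / 1.00 = 1.90 (f = 0.2) or 2.85 (f = 0.3)
- Probability of significance, p = 0.47 or 0.80
- Significant in i.ARTs only, p(1 − p): 0.47 × 0.53 = 0.25 or 0.80 × 0.20 = 0.16

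Simulations gave 0.45-0.49 and 0.79-0.82 for the first probability, and 0.24-0.27 and 0.15-0.17 for the second. Sensitivity to ρ, by the same formulas:

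| ρ | f | significant within i.ARTs | significant in i.ARTs only |
|---|---|---|---|
| 0.3 | 0.2 | 0.36 | 0.23 |
| 0.3 | 0.3 | 0.66 | 0.22 |
| 0.5 | 0.2 | 0.47 | 0.25 |
| 0.5 | 0.3 | 0.80 | 0.16 |
| 0.7 | 0.2 | 0.68 | 0.22 |
| 0.7 | 0.3 | 0.95 | 0.05 |

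With no common fall, the within-i.ARTs test is significant in about 5% of null trials. The problem therefore depends on the visit itself moving the score.

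**3. t test or regression, whichever is significant.** Null simulation, 90 per arm. Counting each item in Table 2 gives 9 sociodemographic + 2 depression/anxiety + 1 substance use + 2 stigma/discrimination + 1 self-efficacy + 2 knowledge/beliefs = 17 moderators. They were assumed to explain 10-40% of the variance.

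- Both tests at .05: about 7-8% (individual runs 6.6-8.5%)
- Regression at .05/17 or .05/6 (6 being the Table 2 moderator rows), t test at .05: about 5%

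The inflation is modest, and it disappears if the Bonferroni sentence covers the arm term.

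**4. What the Bonferroni sentence would do to the arm test.** Step 1 repeated with α divided by the number of moderators:

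- 6 moderators: α = .05/6 = .0083, power about 54%
- 17 moderators: α = .05/17 = .0029, power about 40%

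One hypothesis could thus be tested with about 78% power by the t test, or 40-54% in the adjusted model, depending on how one sentence is read. These powers ignore any precision gained from the covariates.

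**The case against.** A reader might infer that the plan contradicts itself because its primary analysis has an α while its primary outcomes are purely descriptive. The text does not support that. The same paragraph pairs the phrase with a secondary efficacy analysis of treatment actually taken, so primary most naturally means intent-to-treat as against as-treated. Descriptive primary outcomes are acceptable in a pilot, and the plan gives its reason for them.

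A reader might also infer a large inflation from picking between t test and regression, or from adding satisfaction with the chosen method as a second tested outcome. Neither stands. The first is modest and depends on the Bonferroni sentence (step 3). For the second, Study Outcomes and Measures names one secondary outcome, decisional conflict, and the Analysis section does not list satisfaction for comparison.

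The remaining defence is stronger:

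- The sample-size section points to the between-arm t test at .05, so an intended key test can be inferred.
- The model's covariates are listed in Table 2.
- Nothing says a within-arm change will count as an i.ARTs effect.
- A statistical analysis plan, not shown here, could rank the analyses.

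All of this lowers the stakes but does not settle the point. The sample-size section never calls its t test deciding. The Analysis section then adds a later model and within-arm comparisons at the same level, and leaves the final method to the data. This is a matter of what the article states, not of detail left out: it sets competing comparisons side by side and attaches a divisor that does not fit them.

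**Conclusion.** The concern holds in a limited form. The plan lists several comparisons of its sizing outcome, names none as deciding, and leaves the α for the arm effect unclear. The within-arm comparisons are the serious part, because they are not randomised tests of i.ARTs. Under an equal fall of 0.2-0.3 SD in both arms and a correlation of 0.5, the within-i.ARTs test would be significant in roughly 45-80% of null trials, and the pattern of significance in i.ARTs only would occur in about 15-27%.

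These figures rest on assumed falls and correlations. They become false claims only if within-arm results are read as evidence for i.ARTs, which the plan permits but does not announce. The choice between t test and regression is a minor issue, at about 7-8% against 5% at most settings. The documents do not show that any improper claim is intended.

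**What to change.** In the Analysis section:

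1. State that the single inferential test of i.ARTs is the between-arm difference in postvisit Decisional Conflict Scale score, by intent to treat, at two-sided α=.05, from one model specified in advance (for example, a linear model with arm and baseline score).
2. State that the Bonferroni adjustment does not apply to this arm test, only to any tests of moderators.
3. Report the unadjusted t test and the moderator-adjusted model as supportive.
4. Report within-arm changes as means with 95% confidence intervals, without inference about i.ARTs.

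Point 2 is essential. If the divisor stays attached to the arm test, power falls from about 78% to about 54% or 40% (step 4). With points 1 and 2 together, type I error is 5% and power is at least the 78% of step 1. Adjusting for baseline can only help here: at an assumed correlation of 0.5 the residual SD is 17.03 × √(1 − 0.25) = 14.75, the noncentrality is 7/(14.75 × √(2/90)) = 3.18, and power is about 89%.

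The cost is a few sentences before phase 3 begins, with no extra participants or data. What is given up is the option to claim an effect from one of the other tests.

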**Figure 1 figure1:**
[figure not shown]
Study overview. *i.ARTs*: i.ART+support; LAI ART: long-acting injectable ART; MWCCS: MACS/WIHS Combined Cohort Study; WWH: women with HIV.

**Table 1 table1:** Overview of data sources and participants.

Phase	Data source	Participants	Scope of data	Purpose
1	MWCCS^a^ 2020 cohort survey	1500 WWH^b^ at 9 MWCCS sites	WWH perspectives on LAI ART^c^ and decision making; identify relevant barriers and facilitators to LAI ART uptake; characteristics of women who are most likely to adhere to LAI ART	Generate *i.ARTs*^d^ content
1	Provider interviews	45 medical/social service providers at MWCCS sites	Provider perspective on characteristics of women most likely to adhere to LAI ART; reasons providers would not offer LAI ART to a woman for whom it is clinically indicated; provider perceptions of multilevel barriers and facilitators to WWH’s ART use	Generate *i.ARTs* content
2	Focus groups	MWCCS providers, WWH in Miami, Florida	Feedback on successive iterations of *i.ARTs*	Develop and refine *i.ARTs* content
3	Baseline and postvisit survey	180 WWH (90 from the intervention/*i.ARTs* arm and 90 from the control arm)	Information on decisional conflict (baseline and post), acceptability and satisfaction (post only), and sociodemographic and behavioral moderators (baseline only)	Assess *i.ARTs* acceptability and usability outcomes, assess impact of moderators
3	Exit interviews	20 WWH who receive *i.ARTs* and 10 providers	WWH and provider perspectives on *i.ARTs* tool	Assess *i.ARTs* feasibility, usability, acceptability
3	Electronic medical record data	180 WWH	*i.ARTs* adherence data for study participants, including clinic visits, medication refills, and viral load data	Preliminary impact of *i.ARTs* data on treatment-related outcomes

^a^MWCCS: MACS/WIHS Combined Cohort Study.

^b^WWH: women with HIV.

^c^LAI ART: long-acting injectable antiretroviral therapy.

^d^*i.ARTs*: i.ART+support

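### The Bonferroni rule divides α by the number of moderators in the regression; read plainly it falls on the arm effect, where it has no multiplicity basis and does not match the α used for sizing

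*Protocol article*

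**What the plan says.** The Analysis section of the protocol article describes two steps for normally distributed outcomes: a t test between arms, then a multivariable model "with arm membership as the principal covariate, while controlling for the moderators listed in the previous sections and in Table 2". It sets the primary analysis as intent-to-treat, "with α=.05, and 2-sided tests". The next sentence reads: "The number of moderators included in the regression model will be used to make a Bonferroni adjustment" to the α value. It does not name the test to which the adjusted α applies, and it does not give the number of moderators.

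The Power Analysis and Sample Size section bases the trial on decisional conflict, the secondary outcome: "we calculated sample size for α=.05, power=0.8 for an independent samples" t test. It concludes that "the sample size of 90 in each group, for a total of 180, provides 80% power". No divided α appears there.

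Table 1 lists, among the purposes of the Phase 3 surveys, to "assess impact of moderators". Table 2 lists the moderators in six rows.

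**The concern.** Bonferroni divides α by the number of hypotheses tested. The regression described has one coefficient of interest, arm, and the moderators enter as controls. Whether there are two or twenty of them, the arm effect is tested once. The only α in that section is the .05 of the primary analysis, so the natural reading is that this .05 is divided by a covariate count.

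Three consequences follow on that reading:

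- The correction answers no multiplicity in the arm effect.
- The threshold for the arm effect depends on model building. Dropping a covariate loosens it and adding one tightens it.
- The stated 80% power, computed at .05, does not describe the adjusted regression test.

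At stake is the one between-arm comparison on which the trial was sized.

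**Working it through.** **Inputs**
- Power Analysis and Sample Size section: mean 21 (SD 16) in the intervention arm, mean 28 (SD 18) in the control arm, 90 per arm, α=.05, target power 80%.
- Analysis section: two-sided tests, and division of α by k, the number of moderators in the model.
- Table 2, for k: 6 moderator rows, which itemise to 17 variables. These are 9 sociodemographic items plus depression, anxiety, substance use, discrimination, HIV stigma, self-efficacy, ART knowledge and medication beliefs.
- Assumption: no dropout, since the sizing paragraph mentions none.

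**The plan's own figure**
- Pooled SD = √((16² + 18²)/2) = √290 = 17.03.
- Difference = 28 − 21 = 7, so d = 7/17.03 = 0.411.
- Noncentrality = d × √(n/2) = 0.411 × √45 = 2.757, with 178 degrees of freedom.
- At two-sided α=.05, power from the noncentral t is 78.3% (78.7% by the normal approximation). This reproduces the stated 80% to within 2 points. A full 80% needs 94 per arm.

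**The same test at α = .05/k, with 90 per arm and no precision gain from covariates**

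| k | α | Power | n per arm for 80% | Difference detectable with 80% power |
|---|---|---|---|---|
| 1 (undivided) | .0500 | 78.3% | 94 | 7.2 |
| 2 | .0250 | 69.0% | 114 | 7.9 |
| 4 | .0125 | 59.3% | 134 | 8.6 |
| 6 (Table 2 rows) | .0083 | 53.7% | 146 | 8.9 |
| 17 (itemised) | .0029 | 40.1% | 175 | 9.8 |

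**Allowing for precision gained from covariates**

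The rule is tied to the regression, where covariates that predict the outcome shrink the residual SD to 17.03 × √(1 − R²). The document gives no R², so the values below are assumptions (noncentral t, 178 degrees of freedom).

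| Assumed R² | k=1 | k=6 | k=17 |
|---|---|---|---|
| 0.1 | 82.4% | 59.5% | 45.9% |
| 0.2 | 86.6% | 66.1% | 52.8% |
| 0.3 | 90.6% | 73.4% | 61.1% |

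Across this range the divided α keeps power below 80%. It would take an R² of about 0.4 (k=6, 81.2%) or 0.5 (k=17, 81.0%) to return to 80%. At those values the undivided test would have 94.3% or 97.3%.

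**The case against.** The strongest reply is that the sentence never says the arm comparison is the adjusted test. A correction counted in moderators could cover tests of the moderators, and Table 1 does plan to look at their impact. In that case there is a family of tests, Bonferroni is a conventional choice, and the arm test stays at .05 with about 78% power. This stands as a possible reading. It does not rescue the wording, because the only α in view is that of the primary analysis and the model described treats the moderators as controls. For the same reason, a reader who infers that the correction covers tests that are never made goes too far. A condensed article may leave the interaction tests to a fuller document, and their absence here is not counted as a fault.

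Second, the trial was sized on the initial t test, while the rule is attached to the regression. The t test could stand at .05 and the two sections would then coexist. So it does not follow that the stated power and the stated analysis are irreconcilable. What follows is that the 80% does not carry over to the adjusted test if the rule applies to it.

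Third, k is not fixed and covariates may add precision, so a flat statement that power is cut to 40–54% claims more than the document supports. Even at k=6 without gain, a true 7-point difference is detected slightly more often than missed.

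Fourth, this is a pilot. The primary outcomes are analysed descriptively, decisional conflict is secondary, and the rule makes false positives less likely, not more. This bears on severity and is accepted.

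**Conclusion.** The point holds in conditional form. As worded, the rule most naturally divides the α for the arm effect by a number of control covariates. That has no multiplicity basis, makes the threshold depend on covariate selection, and does not match the undivided α=.05 used for sizing.

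If the divided α governs the arm test on decisional conflict, power with 90 per arm drops from about 78% to about 54% (k=6) or 40% (k=17) without covariate gain. With an assumed R² of 0.1 to 0.3 it is about 60–73% (k=6) or 46–61% (k=17). These figures rest on the plan's means and SDs, no dropout, and a reviewer's count of k from Table 2. If the rule is meant only for moderator tests, the arm comparison loses nothing and the fault is one of wording.

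The documents do not support the stronger reading that the trial's power has been shown to be halved. Severity: should fix. The outcome is secondary in a pilot, and the rule errs on the conservative side.

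**What to change.** Replace the Bonferroni sentence in the Analysis section with two statements:

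1. The arm effect on decisional conflict, in both the t test and the adjusted regression, is tested at two-sided α=.05 whatever the number of covariates.
2. Any Bonferroni or false-discovery correction applies only to prespecified exploratory arm-by-moderator interaction tests, with the number of those tests given.

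The first statement brings the Analysis section into line with the sizing paragraph. The second gives the moderator purpose in Table 1 a defined analysis and places the correction where there is a family of tests.

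The cost is one paragraph of wording. It needs no additional participants or data, and it should be settled before any outcome data by arm are seen, because the choice changes the decision threshold.
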